#### Body Composition

The following parameters will be measured: height, weight, body mass index (BMI), body fat percentage, fat mass, visceral fat, lean mass, abdominal fold, contracted arm perimeter, waist perimeter, hip perimeter, and sum of six folds.

Height will be determined with an accuracy of 0.10 cm with a SECA stadiometer (SECA, Hamburg, Germany). Participants will stand erect without shoes, with heels together and their head in the Frankfort horizontal plane. Body weight will be evaluated with an electronic balance with a sensitivity of 0.10 kg (Tanita BC 418 MA, Tanita Corp. Tokyo, Japan). Body mass index will be obtained using the formula: body weight / height^2^. The fat mass, visceral fat and lean mass will be estimated by bioelectrical impedance analysis (BIA) using an eight-contact electrode segmental body composition analyzer (Tanita BC-418, Tanita Corp. Tokyo, Japan).

To assess skinfolds and perimeters, a 0.50 mm sensitivity Slim Guide caliper and a measuring tape (CESCORF) will be used, respectively (90). The muscle mass will be estimated by using the formula of (91).

All measurements will be made in duplicate non-consecutively and using the average value as the final value. All women will be measured at the same time of the day for pre- and post-intervention to avoid errors due to differences in hydration. All analyses will be performed by a level I anthropometric technician certified by the International Society for the Advancement of Kineanthropometry (ISAK) as described in its Reference Manual (92).

#### Blood Test

A full analytical profile will be made to extract different parameters detailed below. The activity of Creatin Kinasa will allow analyzing the muscle damage caused by the exercise (93). High density lipoprotein (HDL) cholesterol and triglycerides will yield information on the presence of metabolic syndrome, understanding this as an association of cardiovascular risk factors (27). Glucose will be measured to analyze the presence of diabetes mellitus and know cardiovascular risk (94). The level of oxidative stress and cardiovascular risk will be known through uric acid (95). Sodium and potassium will be examined to determine if there is an adequate response to the osmotic balance in the body (96). The status of the thyroid gland will be determined by observing the levels of Thyroid Stimulating Hormone (TSH) (97). Finally, Glycohemoglobin A1c (HbA1c) will allow monitoring the evolution of sugar in the months prior to the study (98, 99). The blood tests will be made by the endocrinology department of the Arnau of Vilanova's University Hospital, Lérida, (Spain).

#### International Physical Activity Questionnaire (IPAQ-E)

The IPAQ-E consists of seven open questions in reference to the activities carried out by the elderly in the last 7 days. These questions evaluate the intensity by classifying it into Vigorous Physical Activity (VPA), Moderate Physical Activity (MPA), or Slight Intensity Activities (SPA). They also evaluated the frequency (days per week) as well as the time spent in each of these activities. The Total Physical Activity (TPA) is the sum of the VPA, the MPA, and SPA (100). They are considered VPA those that involve an intense physical effort and that entails breathing much more intensely than normal. MPA requires a physical effort that increases breathing at a somewhat more intense intensity than normal. Slight intensity activities include walking recreationally or for leisure (101). Only activities that last a minimum of 10 min will be considered for registration. The IPAQ-E will allow verifying the untrained condition of the participants since it gives information about the amount of physical activity which they practice in their daily life. At the same time, IPAQ-E will be the control tool regarding the amount of physical activity which the participants will practice in the time run between post-test and follow up.

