## Methods/Design

### Experimental Approach

The study is designed as a blinded two-arm randomized trial with parallel-groups and a follow-up. This study protocol is reported following the SPIRIT guideline for standard protocol items in interventional trials (69). The study protocol is registered in the ISRCTN registry (trial-ID: ISRCTN15558857 (70) where all the important modifications will be recorded.

Participants will be blinded and distributed into two groups by a computer random number generator (71), the voluntary exercise with WB-EMS group (EX + WB-EMS) or the voluntary exercise group (EX). The EX + WB-EMS group will conduct a resistance strength training program with superimposed WB-EMS while the EX group will perform only resistance strength training. Participants will be evaluated at the beginning (baseline), at the end of the 10 weeks of intervention (post-test) and 6 months after the end of the intervention (follow-up) (see Figure 1).

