**Figure 1 F1:**
[figure not shown]
Experimental design diagram.

The sample size was determined by an a-priori power analysis using the G^*^Power3 software for Mac (72) following the indications of Beck (73). The effect size value used was: d = 0.70 with a total sample size of 30, based on a study of WB-EMS training on hip circumference in postmenopausal women (60), with two levels for the between-subject factor (EX+WB-EMS, EX), three levels for the within-subject factor (Baseline, 10 weeks, 6 months), alpha error probability set at 0.05 and a power of 0.80. This analysis indicated a minimum total sample size of 22 participants. Considering a dropout rate of 25%, 14 participants per arm will be required. In order to check the minimum effect size to which the model will be sensitive, a sensitivity analyses with the overestimated sample size assuming a 25% of dropout rate (*n* = 28) was done. The power and alpha values used were 0.80 and 0.05, respectively. The model will be sensitive enough to detect effects as small as d = 0.60.

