### Interventions

Both groups will train with a frequency of 2 weekly sessions. They will have 48 h of rest between sessions. To ensure the blinding of participants, the EX + WB-EMS group will train on Mondays and Thursdays while the EX group will train on Tuesdays and Fridays. Both groups will perform the same program consisting of endurance tasks and resistance strength exercises, but the EX + WB-EMS group will also implement a superimposed WB-EMS during the training. The training protocols will be supervised by two instructors graduated in Physical Activity And Sports Sciences with wide experience in WB-EMS training. Participants were asked not to make physical efforts outside the training program.

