### Statistical Procedures

After checking normality and homogeneity assumptions, the effectiveness of different training programs on quantitative dependent variables will be assessed by a 2 × 2 mixed ANOVA. Group training intervention (“EX+WB-EMS,” “EX”) will be included as between-subjects factor, improvement (“10 weeks from Baseline,” “6 months from Baseline”) will be included as the repeated within-subjects factor, and group ^*^ improvement will be included to account for the interaction effects. Whenever a significant main effect or interaction will be observed, Bonferroni's *post hoc* correction will be used to aid interpretation of these main effects or interactions, either between-subjects factor at whatever time point or within-subjects factor at whatever group (102, 103). Hedge's *g* effect size (*g*) will be calculated and interpreted as follows *g* < 0.20 = trivial, *gfrom*0.20*to*0.50 = *mild, g* from 0.50 to 0.80 = moderate and *g* > 0.80 = large (104). Whenever the data fails to meet assumptions, robust methods will be performed following procedures of (105) and the explanatory measure of effect size (ξ) will be calculated and interpreted as suggested by (106). Values of ξ = 0.10, 0.30, and 0.50 correspond to small, medium, and large effect sizes, respectively. The qualitative ordinal variables will be analyzed with a 2 × 2 rank-based ANOVA following directions from (107). Significance level will be set at α= 0.05. The statistician will be blinded to both groups during data analyses. Intention-to-treat analysis will be performed for the primary and secondary outcomes. If necessary, a multiple imputation technique will be used to handle missing data. All analyses will be performed with JASP (version 0.11.1; JASP Team (2019), University of Amsterdam, the Netherlands) and with statistical software R Core Team (2019) for Mac and WRS2 package (108).

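### The follow-up visit has two possible time origins, and one 7-day recall cannot serve as the activity control for the months between post-test and follow-up

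*Protocol article*

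**What the plan says.** **Timing.** Experimental Approach sets the post-test "at the end of the 10 weeks of intervention (post-test") and the third assessment "6 months after the end of the intervention (follow-up"). The sample-size paragraph in the same section lists "three levels for the within-subject factor (Baseline, 10 weeks, 6 months") without saying from when the six months run. Table 1 has a six-month follow-up column, also without an origin. Statistical Procedures defines the within-subject factor as "improvement (“10 weeks from Baseline,” “6 months from Baseline").

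**Activity measurement.** The IPAQ-E section describes "seven open questions in reference to the activities carried out by the elderly in the last 7 days" and then states that the "IPAQ-E will be the control tool regarding the amount of physical activity which the participants will practice in the time run between post-test and follow", meaning the follow-up visit. Table 1 schedules the questionnaire at baseline (T0), post-study (T2) and follow-up (T3), and at no time between T2 and T3.

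**Use of the IPAQ-E.** The Discussion plans an adherence comparison that sets the pre-training week against the last week before follow-up. Statistical Procedures applies the 2 × 2 mixed ANOVA to the quantitative dependent variables and does not exempt the IPAQ-E.

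**Activity rule.** Interventions says "Participants were asked not to make physical efforts outside the training program". No rule is given for the months after training ends.

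**The concern.** Two things govern what a T3 result means: how long the women have been off training, and what they did in that time.

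On the first, the design and analysis sections give different answers if both are read literally. A visit booked from one section would fall ten weeks away from a visit booked from the other, and detraining depends on elapsed time.

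On the second, the article claims control of activity over the whole interval but names an instrument that looks back one week. Later exercise is expected here: the women are recruited through a sports center, and the Discussion hopes the programme will generate adherence to exercise. A T3 difference, or its absence, could therefore reflect a retained effect, detraining or later exercise. The Discussion also claims to identify the isolated effect of WB-EMS, which makes the attribution matter.

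A smaller, conditional issue arises at T2. If the questionnaire is answered soon after the last session, it counts the trial's own sessions as the women's activity. The 10-week change would then partly measure the intervention.

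**Working it through.** **Inputs.** Intervention 10 weeks and follow-up six months (Experimental Approach; Statistical Procedures). Recall 7 days (IPAQ-E section). Two sessions a week, Monday/Thursday or Tuesday/Friday by arm (Interventions). Sessions of 40 minutes: 10 walking warm-up, 10 strength in two 5-minute blocks, 10 treadmill, 10 stretching (EX Group Intervention; the WB-EMS arm does the same training). The article states no off-training duration in weeks; those below are derived.

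**Step 1: length of the off-training period.**
Six months = 6 × (365.25 / 12) / 7 = 26.1 weeks.

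| Origin | Weeks from baseline | Weeks off training |
|---|---|---|
| End of intervention (Experimental Approach) | 10 + 26.1 = 36.1 | 26.1 |
| Baseline (Statistical Procedures, read literally) | 26.1 | 26.1 − 10 = 16.1 |

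The difference is 10 weeks.

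**Step 2: share of the interval seen by the T3 recall.**
Coverage = 1 week / weeks off training.
- 1 / 26.1 = 3.8%
- 1 / 16.1 = 6.2%

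The T2 recall looks backwards from the start of the interval and adds nothing to this coverage.

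**Step 3: what the T2 recall could contain.** The day of the post-test questionnaire is not stated. Let L be the days from the last session to the questionnaire. The last two sessions are 3 days apart in each arm, so the earlier one lies L + 3 days back.
- L ≤ 4: both sessions are inside the 7 days, 2 × 40 = 80 minutes of session time.
- L from 5 to 7: one session, 40 minutes.
- L > 7: none.

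How many of those minutes would be scored is uncertain, because the IPAQ-E section counts only activities of at least 10 minutes and the strength work is in 5-minute blocks. With both sessions inside the window, warm-up and treadmill alone give 2 × (10 + 10) = 40 minutes, adding strength gives 2 × 30 = 60, and the whole session gives 80.

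**Step 4: is T2 used for the IPAQ-E?** The Discussion's adherence comparison uses only T0 and T3. Table 1 nevertheless collects the IPAQ-E at T2, and the general ANOVA has the 10-week change as one of its two levels. Nothing excludes the IPAQ-E from it.

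**The case against.** **The label may be harmless.** The ANOVA factor is called improvement, so its second level can be read as the change from baseline to the six-month visit. Only Experimental Approach actually defines that visit. This is a fair reading, and it makes the conflict an ambiguous label rather than two stated dates. It does not remove the need to align them: the companion label's 10 weeks is time elapsed from baseline, and the sample-size paragraph puts 10 weeks and 6 months on one axis.

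**The follow-up comparison survives.** A reader might infer that the follow-up question cannot be answered at all. The documents do not support that. The Background words no separate retention or detraining objective, and the randomised between-arm contrast at T3 remains valid as the effect of assignment, provided both arms are seen at the same time. Activity after T2 is post-randomisation; measuring it poorly limits explanation but does not void the comparison.

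**The T2 problem is conditional.** A reader might infer that a large artificial rise at T2 is certain, or that the added current would shift identical sessions from moderate to vigorous in one arm. Neither is established. The questionnaire day is not given, the planned session volume is equal in both arms, supervised exercise is real activity, and nothing in the article shows that current changes the perceived breathing on which the IPAQ-E classes intensity. What stands is that the general ANOVA does not exclude T2.

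**The Discussion is already accurate about T3.** It describes that recall as the week before follow-up. This supports narrowing the IPAQ-E section to match.

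**Conclusion.** The point holds in a limited form and should be corrected before analysis.

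- The follow-up origin is inconsistent on a literal reading: about 26 against about 16 weeks off training. These weeks are derived by taking six months as 26.1 weeks; the article does not write them.
- One 7-day recall covers about 4% to 6% of the post-test to follow-up interval. It describes the week before T3 and cannot separate a retained effect from detraining or later exercise.
- If the T2 questionnaire is completed within 7 days of the last session, its recall includes one or two supervised sessions, and the 10-week IPAQ-E change partly records the intervention. With a longer lag this falls away.

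The randomised comparison at T3 is not invalidated. What is lost is the basis for attributing a T3 difference, or its absence, to persistence or fading of the training effect.

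**What to change.** 1. **One origin.** Reconcile Experimental Approach and Statistical Procedures, use the same origin in the sample-size paragraph and Table 1, and label the second ANOVA level as the change from baseline to that visit.
2. **IPAQ-E at T2.** Either tell participants to leave supervised sessions out of their post-test answers, or omit T2 from the IPAQ-E analysis. Keep the baseline-to-follow-up comparison planned in the Discussion.
3. **The control claim.** Withdraw it. Say that the T3 IPAQ-E describes only the week before follow-up, and that T3 results show the effect of assignment under free activity.

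All three are wording changes, with at most one added instruction on the T2 questionnaire, and need no extra participants or visits. Repeated recalls between T2 and T3 would give better information on that interval, but they take resources and are optional once the claim is narrowed.

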### Statistical Procedures

After checking normality and homogeneity assumptions, the effectiveness of different training programs on quantitative dependent variables will be assessed by a 2 × 2 mixed ANOVA. Group training intervention (“EX+WB-EMS,” “EX”) will be included as between-subjects factor, improvement (“10 weeks from Baseline,” “6 months from Baseline”) will be included as the repeated within-subjects factor, and group ^*^ improvement will be included to account for the interaction effects. Whenever a significant main effect or interaction will be observed, Bonferroni's *post hoc* correction will be used to aid interpretation of these main effects or interactions, either between-subjects factor at whatever time point or within-subjects factor at whatever group (102, 103). Hedge's *g* effect size (*g*) will be calculated and interpreted as follows *g* < 0.20 = trivial, *gfrom*0.20*to*0.50 = *mild, g* from 0.50 to 0.80 = moderate and *g* > 0.80 = large (104). Whenever the data fails to meet assumptions, robust methods will be performed following procedures of (105) and the explanatory measure of effect size (ξ) will be calculated and interpreted as suggested by (106). Values of ξ = 0.10, 0.30, and 0.50 correspond to small, medium, and large effect sizes, respectively. The qualitative ordinal variables will be analyzed with a 2 × 2 rank-based ANOVA following directions from (107). Significance level will be set at α= 0.05. The statistician will be blinded to both groups during data analyses. Intention-to-treat analysis will be performed for the primary and secondary outcomes. If necessary, a multiple imputation technique will be used to handle missing data. All analyses will be performed with JASP (version 0.11.1; JASP Team (2019), University of Amsterdam, the Netherlands) and with statistical software R Core Team (2019) for Mac and WRS2 package (108).

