Unfortunately, the high risk of bias of some of the previous studies leads to little evidence regarding the effectiveness of training with WB-EMS (68). So, there is a need for new studies which ensure the use of protocols compatible with a rigorous scientific methodology. The objective of this study is to analyze, from a broad and multivariable perspective, the influence of a 10-weeks WB-EMS training program on the physical condition and health of postmenopausal women using a 2-arm parallel group design with follow-up.

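### The 2 × 2 ANOVA on change scores is unbiased, but none of its omnibus tests is the 10-week group effect; a baseline-adjusted 10-week contrast tested directly would usually be stronger at little cost

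*Protocol article*

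**What the plan says.** The objective, at the end of the Background, is to study "the influence of a 10-weeks WB-EMS training program on the physical condition and health of postmenopausal women" in a two-arm design with follow-up. The closing summary of the Discussion again speaks of the effect after the 10-week intervention. No primary outcome or primary time point is named.

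Under Experimental Approach, women are assessed at baseline, then "at the end of the 10 weeks of intervention (post-test) and 6 months after the end of the intervention (follow-up"). No study training is described between those last two visits; the IPAQ-E section says only that activity in that interval will be recorded.

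Statistical Procedures states that "the effectiveness of different training programs on quantitative dependent variables will be assessed by a 2 × 2 mixed ANOVA", with group as the between-subjects factor, while "improvement (“10 weeks from Baseline,” “6 months from Baseline”) will be included as the repeated within-subjects factor". A group-by-improvement interaction is included and no baseline covariate is named. Bonferroni comparisons follow "Whenever a significant main effect or interaction will be observed", and cover "either between-subjects factor at whatever time point or within-subjects factor at whatever group".

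The sample-size paragraph under Experimental Approach uses d = 0.70, two groups and three time levels including baseline. It gives 22 women in total, raised to 14 per arm.

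**The concern.** Each omnibus test answers a question other than how the arms differ at the end of training:

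- **Group** tests the average of the 10-week and follow-up changes.
- **Improvement** compares the two changes with each other. It does not test change from baseline.
- **Group × improvement** tests whether the group difference moves between the two visits. Baseline cancels: (Y6m − Y0) − (Y10w − Y0) = Y6m − Y10w. A benefit that is fully kept leaves this term null.

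The arms are compared at 10 weeks only in a second step, at a reduced significance level. Baseline is used only by subtraction, which is less precise than using it as a covariate unless the correlation with the later value is close to 1. With 14 per arm, avoidable loss of power on the question the objective asks is worth removing.

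Two mismatches need no calculation. Statistical Procedures dates the second level 6 months from baseline, whereas Experimental Approach puts the visit 6 months after a 10-week intervention, about 10 + 26 = 36 weeks from baseline. The power calculation has three time levels, but the analysis has two changes.

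**Working it through.** **The plan's own figure.** The article gives neither the correlation among visits nor the effect that was powered, so 22 cannot be fixed from its stated inputs. Take f = d/2 = 0.35. For the within or interaction test, λ = f²·N·m/(1 − rho). With m = 3 levels and rho = 0.25, N = 22 gives λ = 0.1225 × 22 × 3/0.75 = 10.8 and power 0.815. The sensitivity at N = 28 is then d = 0.604, which matches the stated 0.60. So the figures are attainable for an interaction or within-subject test with rho about 0.25–0.27. At rho = 0.5 with sphericity the interaction would need 16 and the between-group test 46; at N = 22 the between-group test has power 0.48. The calculation therefore does not describe a 10-week group comparison.

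**Inputs for the comparison.** From the article: 14 per arm, d = 0.70, α = 0.05. Assumed: d is the 10-week group difference in SD units; SD 1 at every visit; equal correlation rho among the three visits; a fraction r of the 10-week effect kept at follow-up; Bonferroni over the two time points (0.025 each).

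**Per-woman error variance and effect tested**

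- Group term: variance 1.5(1 − rho), effect 0.70(1 + r)/2
- Interaction: variance 2(1 − rho), effect 0.70(1 − r)
- 10-week change score: variance 2(1 − rho), effect 0.70
- 10-week ANCOVA: variance 1 − rho², effect 0.70

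The ANCOVA to change-score variance ratio is (1 + rho)/2, that is 0.75, 0.85 and 0.90 at rho 0.5, 0.7 and 0.8.

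Noncentrality is effect/√(2 × variance/14). At rho = 0.5 the 10-week change score gives 0.70/√(2 × 1.0/14) = 1.85. ANCOVA gives 0.70/√(2 × 0.75/14) = 2.14, as does the group term with r = 1.

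**Power** (noncentral t, and simulation with 40,000 trials per setting for the post hoc route and ANCOVA)

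| Test | rho 0.5 | rho 0.7 | rho 0.8 |
|---|---|---|---|
| Group term, r = 1 / 0.5 / 0 | 54 / 34 / 18% | 76 / 51 / 27% | 90 / 69 / 37% |
| Interaction, r = 1 / 0.5 / 0 | 5 / 15 / 43% | 5 / 21 / 63% | 5 / 29 / 80% |
| Planned 10-week post hoc route | 29–31% | 48–51% | 68–70% |
| 10-week change score, 0.025, no omnibus condition | 32% | 51% | 71% |
| 10-week change score, 0.05 | 43% | 63% | 80% |
| 10-week ANCOVA, 0.05 | 52% | 69% | 83% |

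The post hoc route was simulated as opening after a significant group or interaction term. The improvement term would open it too, but the route can never exceed the 0.025 row, so that adds at most about 3 points.

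**Where the gain comes from at rho = 0.5.** Dropping the omnibus condition moves power from 29–31% to 32%, testing at 0.05 to 43%, and adjusting for baseline to 52%. Baseline adjustment alone is worth about 9, 5 and 2–3 points at rho 0.5, 0.7 and 0.8.

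**Break-even with the group term.** Equating noncentralities gives r = 2√(1.5/(1 + rho)) − 1, which is 1.00, 0.88 and 0.83. Above that retention the planned group term is the stronger test.

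**With 11 per arm** (22 in total) and rho = 0.5: ANCOVA 42%, post hoc route about 22%, group term 44 / 27 / 15%.

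**The case against.** A reader might infer that the plan ignores baseline, is invalid, or never tests the arms at 10 weeks. The text supports none of these. Both repeated levels are changes from baseline. In a randomised trial a change-score comparison is unbiased, so only precision is at stake. Comparison of the arms at each time point is expressly provided for, if only conditionally.

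A reader might also credit the whole gap, such as 29–31% against 52%, to baseline adjustment. Roughly half or more of it comes from comparing a test at 0.025 with one at 0.05. At equal α of 0.025 and rho = 0.5, ANCOVA has 42% against 32% for the change score (noncentral t, which runs 1–2 points above simulation for ANCOVA).

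Nor is averaging the visits always a loss. If the benefit is fully kept, the group term equals ANCOVA at rho = 0.5 and beats it by about 7 points at rho 0.7–0.8 (76% against 69%, 90% against 83%). The article gives neither the correlation nor the expected retention, and its objective includes follow-up, so 10 weeks as the main time point is an inference.

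Finally, the standard ANOVA would drop a woman who misses only the follow-up visit, but intention-to-treat analysis and multiple imputation are already stated, so this adds little.

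These points stand, and they limit the concern to efficiency and to clarity about which contrast answers the question. They do not remove it. The group term's advantage needs a largely sustained effect six months after training, and even then it estimates an average of two visits.

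**Conclusion.** A recommended improvement, not an error that invalidates the analysis. No omnibus term is the 10-week group effect, the interaction rejects at only 5% when the benefit is fully kept, and the 10-week comparison comes second and at a reduced level.

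Against that route, a direct baseline-adjusted 10-week test gains about 13–23 points at any retention, for 14 per arm, d = 0.70 and rho 0.5–0.8. Against the planned group term it gains about 14–18 points if half the effect remains at follow-up and 34–46 points if none remains. It gains nothing, or loses about 7 points, if all remains. Correlation, retention and the Bonferroni family are assumptions.

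The change does not rescue the sample size: at rho = 0.5 the better test still reaches only 52%. The follow-up label and the time levels in the power calculation are inconsistent whatever these assumptions are.

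**What to change.** For each quantitative outcome, replace the 2 × 2 ANOVA by a linear mixed model on the 10-week and follow-up values. Include baseline value, group, visit, group × visit and baseline × visit, with unstructured within-person covariance. ANCOVA at each visit is a simpler alternative. Name the baseline-adjusted group difference at 10 weeks as the main contrast, tested directly at 0.05 with no prior omnibus test. Make the follow-up difference a separate secondary contrast.

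Reconcile the label of the second level in Statistical Procedures with the visit timing in Experimental Approach. Redo or restate the power calculation for the contrast actually analysed, giving the assumed correlation.

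The cost is a few lines of text and one degree of freedom for baseline; R is already named. The trade-off is about 7 points less power than the planned group term if the benefit is fully kept and rho is 0.7–0.8. The choice should be recorded before any unblinded analysis.

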**ASSESSMENTS**					
Physical fitness: Balance, leg flexibility, arm flexibility, leg strength, arm strength, agility, speed, cardiovascular endurance		x		x	X
Mean velocity (m·s-1) and the mean power of exertion (w)		x		x	x
Body composition: Weight (kg), height (cm), body mass index, body fat percentage, fat mass (kg), Visceral fat (kg), lean mass (kg), Abdominal fold, Contracted arm fold, waist perimeter, hip perimeter and Sum six folds (%).		x		x	X
Blood test: Creatin Kinasa, HDL cholesterol and triglycerides, Sodium and potassium, Thyroid Stimulating Hormone (TSH), Glycohemoglobin A1c (HbA1c)		x		x	X
Lifestyl & Health behavior: Physical activity questionnaire (IPAQ): Vigorous physical activity (AFV), Moderate physical activity (AFM) or Walking		x		x	x

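### The arms are compared on change from baseline with no baseline covariate, which costs precision and carries part of any chance baseline difference into the arm contrasts unless the baseline-to-follow-up correlation is about 0.9 or higher

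*Protocol article*

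**What the plan says.** The Statistical Procedures section of the protocol article fixes the model and its terms. It states that "the effectiveness of different training programs on quantitative dependent variables will be assessed by a 2 × 2 mixed ANOVA". Training group is the between-subjects factor, "improvement (“10 weeks from Baseline,” “6 months from Baseline”) will be included as the repeated within-subjects factor", and the product of group and "improvement will be included to account for the interaction effects". The response is therefore change from baseline at two visits. No baseline covariate is listed, and none is named for the robust alternative.

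Baseline values will be available. Under Experimental Approach, "Participants will be evaluated at the beginning (baseline), at the end of the 10 weeks of intervention (post-test) and 6 months after" the intervention ends, and Table 1 marks a baseline measurement for each assessment it schedules. Participants are "distributed into two groups by a computer random number generator", and no balancing on baseline outcome values is described.

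The sample-size paragraph under Experimental Approach gives "The effect size value used was: d = 0.70 with a total sample size of 30", three within-subject levels, alpha 0.05 and power 0.80. It continues: "This analysis indicated a minimum total sample size of 22 participants". This becomes 14 per arm after allowance for dropout, with a detectable d of 0.60 at n = 28. No correlation among repeated measures and no nonsphericity value is given.

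**The concern.** A change score removes baseline with a slope of exactly 1. When baseline and follow-up are imperfectly correlated, the best slope is below 1, so subtraction over-corrects. This has two consequences. The arm contrast has a larger variance than it needs to have. In addition, if one arm happens to start worse, regression to the mean makes that arm's change look better. Both change scores share the same baseline value, so averaging them in the group main effect does not remove the problem.

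At 11 to 14 women per arm, precision is the trial's main limit. The group main effect and the per-visit arm contrasts are the terms that show whether WB-EMS adds anything to exercise alone, so a loss there bears directly on the trial's question.

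**Working it through.** **Inputs.** From the protocol: 14 per arm (N = 28), 11 per arm before the dropout allowance (N = 22), a planned effect of 0.70 SD and alpha 0.05. Assumed: unit outcome variance at each visit, equal correlation r between any two visits, and the same 0.70 SD effect at both follow-ups. r is not in the document, so a range is used.

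**Does the sample-size paragraph fix r?** I reproduced it as a group by time interaction with 2 groups, 3 visits and f = d/2 = 0.35. Noncentrality is f² × N × 3 × ε/(1-r), where ε is the nonsphericity correction.

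| r | ε | N for 80% power | detectable d at n = 28 |
|---|---|---|---|
| 0.25 | 1 | 22 | 0.60 |
| 0.3 | 0.9 | 22 | 0.61 |
| 0.4 | 0.75 | 22 | 0.60 |
| 0.5 | 0.6 | 22 | 0.59 |
| 0.5 | 1 | 16 | 0.49 |

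The published pair (22 and 0.60) follows from r of about 0.25 if sphericity is assumed, and about equally well from higher r with ε below 1. It does not determine r.

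**Variance of the group effect averaged over both visits** (per woman; the arm contrast multiplies it by 2/n):
- change score: 1.5(1-r)
- baseline-adjusted: (1-r)(1+2r)/2, times 1 + 1/(N-4) for estimating the slope. At N = 28 this factor is 1 + 1/24 = 1.042.
- ratio of adjusted to change: (1+2r)/3 × 1.042

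Worked at r = 0.5: change variance 0.75, standard error √(0.75 × 2/14) = 0.327. Adjusted variance 0.50 × 1.042 = 0.521, standard error √(0.521 × 2/14) = 0.273. Ratio 0.69.

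Power comes from the noncentral t with noncentrality 0.70/SE, on N-2 = 26 df (change) and N-3 = 25 df (adjusted).

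| r | variance ratio, N = 28 | power, change score | power, adjusted |
|---|---|---|---|
| 0.25 | 0.52 | 39% | 64% |
| 0.5 | 0.69 | 54% | 69% |
| 0.7 | 0.83 | 76% | 83% |
| 0.9 | 0.97 | above 99% | above 99% |

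**One visit alone.** The ratio is (1+r)/2 × [1 + 1/(N-4)]. At N = 28 it is 0.78 at r = 0.5, 0.89 at r = 0.7 and 0.99 at r = 0.9. Power goes from 43% to 52% at r = 0.5 and from 63% to 69% at r = 0.7. Setting the ratio to 1 gives a break-even r of 0.89 at N = 22 and 0.92 at N = 28.

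**Effect of a chance baseline difference.** Its SD is √(2/n): 0.38 outcome SD at 14 per arm and 0.43 at 11. The probability that it exceeds 0.5 SD in absolute value is 19% at 14 per arm and 24% at 11. The change-score contrast moves by -(1-r) times the difference, so a 0.5 SD difference at r = 0.7 moves it by 0.3 × 0.5 = 0.15 SD, about a fifth of 0.70. The mean absolute difference is smaller, 0.30 to 0.34 SD, which moves the contrast by 0.09 to 0.10 SD at r = 0.7. Simulation (40,000 trials per setting) gave slopes of the change contrast on the baseline difference of about -0.50, -0.30 and -0.10 at r = 0.5, 0.7 and 0.9, and about 0 for the adjusted contrast.

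**Interaction.** (6-month value - baseline) - (10-week value - baseline) = 6-month value - 10-week value. Baseline cancels, so this test is unaffected.

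**The case against.** The planned analysis is valid. Change from baseline already adjusts for baseline, with a fixed slope, and under randomisation its arm contrast is unbiased on average. A reader might infer that the plan ignores baseline, or that its WB-EMS estimate is biased. Neither is supported: what is missing is an estimated slope, and the shift exists only conditionally on the imbalance that happens to occur. Nor is a large imbalance the usual case, since a difference above 0.5 SD is expected in 19% to 24% of trials.

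A reader might also infer from the sample-size paragraph that the plan itself assumes r of about 0.25, where the change score (variance 2(1-r) = 1.5) would be noisier than the unadjusted follow-up value (variance 1). The document does not support this. It states neither r nor a sphericity assumption, and r = 0.4 or 0.5 with ε below 1 gives about the same figures. The row for r = 0.25 is one scenario, and the most favourable to this point.

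The gain also shrinks as r rises. For very stable outcomes it disappears, and at N = 22 with r = 0.9 the single-visit adjusted contrast is marginally less precise (ratio 1.003).

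All of this stands as a limit on size and scope. It does not remove the point: the model and its terms are stated in the protocol, baseline is to be measured, and for r between 0.5 and 0.7 the improvement is material at no cost in data.

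**Conclusion.** The point holds as a recommendation on efficiency and robustness, not as a charge of invalidity. With 14 per arm, the baseline-adjusted group effect has about 0.52, 0.69, 0.83 and 0.97 times the variance of the change-score effect at r = 0.25, 0.5, 0.7 and 0.9. A chance baseline difference of 0.5 SD would move the change-score contrast by 0.15 SD at r = 0.7. The consequence is confined to the group main effect and the per-visit arm contrasts. These sizes rest on an assumed r, equal correlation between visits and the same effect at both visits. The direction is secure for any r below about 0.9; the amount for a given outcome cannot be read from the document. The change should be made.

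**What to change.** For each quantitative outcome, replace the 2 × 2 ANOVA on change scores with a model for the 10-week and 6-month values (or changes; with baseline in the model the arm contrasts are the same). Include arm, visit, arm by visit, baseline and baseline by visit, with a within-woman covariance. Report the baseline-adjusted between-arm difference with a 95% CI at each visit. Where assumptions fail, name a robust version that also carries baseline as a covariate, so that the fallback does not revert to unadjusted change.

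The cost is a few sentences in Statistical Procedures and one degree of freedom for the slope at each visit. No extra measurement or participant is needed, and R is already planned. For outcomes with r near 0.9 or above there is no gain and, at this sample size, possibly a very slight loss.
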